# Treatment of subjects and clinical study procedures

Description of the treatments

All patients in the MB-AS group will receive for 3 days twice daily (morning and evening) 10mg/kg MB accompanied by once daily (morning) 4mg/kg artesunate (= 4mg/kg total daily dose).

MB will be given according to the following weight table:

10,0 – 16,0 kg = 130mg = 2 tablets per treatment = 2 x 2 tablets /day

16,5 – 22,5 kg = 195mg = 3 tablets per treatment = 2 x 3 tablets/ day

AS will be given according to the following weight table:

10,0 – 16,0 kg = 50mg = 1 tablet per treatment = 1 tablet per day

16,5 – 22.5 kg = 100mg = 2 tablets per treatment = 2 tablets per day

AQ will be given according to the following weight table:

10,0 – 16,0 kg = 100mg = 1 tablet per treatment = 1 tablet per day

16,5 – 22.5 kg = 200mg = 2 tablets per treatment = 2 tablets per day

Product description

MB (Urolene Blue®, Star Pharmaceuticals, USA); 1 tablet Urolene Blue® = 65mg)

AS (Artesunate®, Guilin Pharmaceuticals Co., Ltd., China; 1 tablet Artesunate® = 50mg)

AQ (taken from the essential drug store of the Ministry of Health, Burkina Faso; 1 tablet amodiaquine=100mg)

Concomitant treatments

Patients having received antimalarial treatment prior to inclusion (last three days) will be excluded except children having been treated with chloroquine.

All children having fever ≥ 38.5°C will receive standard doses of paracetamol (= acetaminophen; 10 mg/kg) until symptoms subside (taken from the essential drug stock of the Ministry of Health, product description: paracetamol tablets or syrup).

All indicated drugs are allowed, except other western antimalaria drugs, antibiotics with antimalarial efficacy, acetanilide and phenacetin, nalidixic acid, niridazole, nitrofurantoins and sulphonamides (or any other drug that might induce haemolysis in G6PD deficient individuals) from beginning of treatment until end of follow-up.

Prior and concomitant illnesses

History of prior illnesses will become investigated and recorded. All relevant concomitant illnesses will be recorded based on the examination of the study physicians at D0, D1, D2, D3, D7, D14 and D28.

Procedures for monitoring subject compliance

Drug intake will be directly monitored by a study nurse or a field worker for the whole treatment period, supervised by the study physicians.

Visits and treatment schedule

After identification of febrile children in the specified age group in the community, enrolled children are treated and supervised as outpatients according to the study flow explained in chapter 3. Children are examined at regular intervals (D0, D1, D2, D3, D7, D14 and D28) by a study physician. In case of not coming to the clinic on respective examination days, children will be visited at home by field staff. Parents/guardians are instructed to return to the hospital in case of worsening of their child’s clinical condition at any time during the follow-up period.

Day 0

- Presentation of the febrile child at one of the fever measurement points
- Informed consent
- Baseline status (weight, temperature)
- Examination 1 (at the Nouna district hospital)
- Questioning for inclusion/exclusion criteria
- Capillary blood sample for a thin and thick blood film (malaria) and haematocrit
- 1 filter paper is kept for genotypic determination of G6PD deficiency
- 1 filter paper is kept to distinguish between recrudescence and reinfection according to PCR during follow-up
- Treatment 1 (before 14:00) – MB-AS or MB-AQ or AS-MB
- Treatment 2 (evening) – MB

Day 1

- Examination 2 (morning)
- Treatment 3 (morning) – MB-AS or MB-AQ or AS-MB
- Treatment 4 (evening) – MB

Day 2

- Examination 3 (morning)
- Capillary blood sample (parasitemia and haematocrit)
- Treatment 5 (morning) – MB-AS or MB-AQ or AS-MB
- Treatment 6 (evening) – MB

Day 3

- Examination 4 (morning)
- Capillary blood sample (parasitemia and haematocrit) (morning)

Day 7, 14 and 28

- Examination 5, 6 and 7 respectively (morning)
- Capillary blood sample for parasitemia and haematocrit

Other time periods

- Phaenotypical G6PD determination and further investigations according to study physicians judgement will take place at any day between D0 and D28 in case of haemolysis
- 1 filter paper is kept to distinguish between recrudescence and reinfection according to PCR during follow-up (D7, 14, 28 and any other day the child returns for examination between D3 and D28)

Clinical management of (serious) adverse events

Study physicians and emergency medications will be available 24h to deal with SAEs. Additional laboratory tests are available 24h if needed and a standard blood transfusion service is established at the hospital (e.g. in case of haemolysis).

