# Protocol summary

Title: Safety and efficacy of methylene blue combined with artesunate or amodiaquine for malaria treatment in children of Burkina Faso: a pilot study in the frame of the A8 Project of the SFB 544

Design: Single-centre, randomized controlled study in children with uncomplicated falciparum malaria in the Nouna Health District, north-western Burkina Faso

Phase: Phase II

Objectives: The primary objective of this trial is to study the safety of the combination methylene blue (MB)-artesunate (AS) and MB-amodiaquine (AQ) given over three days in 3-4 years old children with uncomplicated falciparum malaria in an area of high malaria transmission intensity compared to the safety of a three days AS-AQ regimen. Secondary objectives are to investigate the efficacy of MB-AS and MB-AQ.

Population: Children aged 3-4 years with uncomplicated malaria from Nouna town.

Sample size: N= 180 (n=60 for each group).

Treatment: The participants in the MB-AS group will receive orally twice daily 10mg/kg MB combined with once daily 4mg/kg AS over 3 days. The participants in the MB-AQ group will receive orally twice daily 10mg/kg MB combined with once daily 10mg/kg AQ over 3 days. The participants of the comparator group will receive a 3 day regimen of once daily oral AS (4mg/kg) combined with once daily AQ (10mg/kg).

Endpoints: The primary endpoint is the number of adverse events (AE) after drug intake until day 28. Secondary endpoints are the number of serious adverse events (SAE), adequate clinical and parasitological response (ACPR) rate on day 28, clinical and parasitological failure rates on day 3, 7, 14 and 28, changes in haemoglobin/haematocrit until day 28, and fever and parasite clearance time.

Study duration and dates: The study will be implemented during the rainy season of the year 2006 (July - October).

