# Trial objectives and purpose

The purpose of the study is to investigate the safety and efficacy profile of the combinations MB-AS and MB-AQ in comparison with AS-AQ in African children with uncomplicated falciparum malaria.

The primary objective of this study is:

- To investigate the safety of the combinations MB-AS and MB-AQ in children with uncomplicated malaria caused by *Plasmodium falciparum*

Justification: MB, AS, AQ and AS-AQ have been shown to be safe in the target population. However, to treat children with the combination of MB-AS or MB-AQ is new. Thus, all adverse events of these new combinations are of interest. The comparison with AS-AQ, the new official first-line treatment for uncomplicated malaria in Burkina Faso, will help to judge the safety of MB-AS and MB-AQ in the study population. This trial should give the necessary information about the safety of the combination MB-AS and/or MB-AQ for judgment and planning of future phase III trials.

The secondary objective of this study is:

- To investigate the efficacy of MB-AS and MB-AQ

Justification: The combination MB-chloroquine has been shown to be effective against malaria in the Nouna study population. However a high rate of recrudescences was observed due to high background resistance to CQ (Meissner, unpublished). Therefore alternative drug combinations with MB need to be identified. There is now sufficient evidence from in vitro and animal models for existence of synergy between the two short acting drugs MB and AS (Akoachere et al. 2005, Barker et al. 2005). Thus AS seems to be an ideal partner drug to MB but it remains to be shown that MB-AS is sufficiently safe and effective when given over a period of three days. Alternatively, the combination MB-AQ could still be sufficiently effective even in areas of high resistance against chloroquine. This trial should give the necessary information about the efficacy of the combinations MB-AS and MB-AQ for judgment and planning of future phase III trials.

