# Selection and withdrawal of subjects

Sample size

180 children (60 children in each of the three different treatment regimens) will be enrolled into the study. The sample size of 60 per arm enables us to demonstrate a difference in AE rates of 10 % with 90% power and at a 0.05 significance level.

Inclusion criteria

- 3-4 year (36-59 months) old children
- Between 10 kg and 22.5 kg body weight
- Ability to swallow tablets
- Uncomplicated malaria caused by *P. falciparum*
- Asexual parasites ≥ 2000/µl and ≤ 200000/µl
- Axillary temperature ≥ 37.5°C
- Burkinabe nationality
- Informed consent

Exclusion criteria

- Complicated or severe malaria
- Any apparent significant disease
- Anaemia (haematocrit < 21%)
- Treated in the same trial before
- Antimalarial treatment prior to inclusion (last three days), except children having been treated with chloroquine

Withdrawal criteria

Participants may be withdrawn from the study at their guardians request and any change in the patient’s condition which in the investigator’s opinion, for reasons of safety or ethics, precludes further participation in the trial. In case of vomiting after the repeated drug intake (one repetition only) of the first drug ingestion, the participant will be withdrawn from the study. Subjects withdrawn from the study during the first 3 days will be replaced.

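### The weight tables do not deliver the stated amodiaquine (10 mg/kg) and artesunate (4 mg/kg) doses: amodiaquine runs low up to 16 kg, artesunate runs high from 16.5 kg

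*Protocol*

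**What the plan says.** The Protocol summary states the doses per kilogram. The methylene blue (MB) plus AQ arm receives "once daily 10mg/kg AQ over 3 days", and the AS-AQ comparator receives "once daily oral AS (4mg/kg) combined with once daily AQ (10mg/kg". The section Treatment of subjects and clinical study procedures repeats the AS dose for the MB-AS arm as "once daily (morning) 4mg/kg artesunate (= 4mg/kg total daily dose". It states no mg/kg figure for AQ.

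The same section then gives one two-row table per drug. For AQ the lower row is "10,0 – 16,0 kg = 100mg = 1 tablet per treatment = 1 tablet per day"; the upper row, 16.5 to 22.5 kg, is 200 mg. For AS the lower row is 50 mg and the upper row is "16,5 – 22.5 kg = 100mg = 2 tablets per treatment = 2 tablets per day". The Product description agrees with these counts ("1 tablet amodiaquine=100mg"; 50 mg for AS). The inclusion criteria admit children "Between 10 kg and 22.5 kg body weight", so both rows apply in full. Nowhere are the mg/kg figures called nominal or approximate, and no accepted range is given.

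**The concern.** Rounding to whole tablets normally scatters the dose on both sides of its target. Here one row of each partner drug lies wholly on one side: AQ low in lighter children, AS high in heavier ones. The regimen named as the comparator is therefore not the regimen the tables prescribe.

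This matters because the trial is meant to provide "necessary information about the safety of the combination MB-AS and/or MB-AQ for judgment and planning of future phase III trials", and the introduction makes AS-AQ the standard of care against which the MB combinations are judged. If the results are described by the stated doses, adverse events and ACPR will be attached to doses that the tables give at very few weights. A phase III trial built on the stated figures would not repeat the regimens tested here.

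**Working it through.** **Inputs.** Stated daily doses: AQ 10 mg/kg and AS 4 mg/kg; MB 10 mg/kg per dose, twice daily (Protocol summary). Tablet amounts and weight rows: Description of the treatments. Eligible weights: 10 to 22.5 kg (Inclusion criteria).

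**Delivered dose** = mg in the row ÷ body weight, at both ends of each row.

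| Drug (target, mg/kg) | Row (kg) | Delivered (mg/kg) | Departure from target |
| --- | --- | --- | --- |
| AQ (10) | 10.0–16.0 | 100/10 = 10.0 to 100/16 = 6.25 | 0% to −37.5% |
| AQ (10) | 16.5–22.5 | 200/16.5 = 12.1 to 200/22.5 = 8.9 | +21% to −11% |
| AS (4) | 10.0–16.0 | 50/10 = 5.0 to 50/16 = 3.1 | +25% to −22% |
| AS (4) | 16.5–22.5 | 100/16.5 = 6.1 to 100/22.5 = 4.4 | +52% to +11% |
| MB (10 per dose) | 10.0–16.0 | 130/10 = 13.0 to 130/16 = 8.1 | +30% to −19% |
| MB (10 per dose) | 16.5–22.5 | 195/16.5 = 11.8 to 195/22.5 = 8.7 | +18% to −13% |

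The stated AQ dose is met exactly only at 100/10 = 10.0 kg and 200/10 = 20.0 kg. The stated AS dose is met only at 50/4 = 12.5 kg; the upper row would meet it at 100/4 = 25 kg, outside the eligible range.

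**Ratio check, which needs no weight distribution.** Tables: 100/50 = 2 and 200/100 = 2. Stated: 10/4 = 2.5. A child given both drugs can match one stated dose at most.

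**Three-day totals.** AQ runs from 3 × 100/16 = 18.8 to 3 × 200/16.5 = 36.4 mg/kg, against a nominal 30. AS runs from 3 × 50/16 = 9.4 to 3 × 100/16.5 = 18.2 mg/kg, against 12.

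**Why the rows miss.** Two adjacent tablet doses are equally far from target at weight (dose 1 + dose 2) ÷ (2 × target):

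- MB: 325/20 = 16.25 kg
- AQ: 300/20 = 15.0 kg
- AS: 150/8 = 18.75 kg

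All three drugs share the break between 16.0 and 16.5 kg, which suits only MB.

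**How much a different whole-tablet break could recover.** Below 15 kg, one AQ tablet is already the nearest whole-tablet dose. Moving the AQ break to 15.0 kg changes the worst shortfall from 37.5% to 33% (100/15 = 6.67 mg/kg) and raises the worst excess from 21% to 33% (200/15 = 13.3 mg/kg). For AS, the table picks the farther whole-tablet dose between 16.5 and 18.75 kg: two tablets give 6.1 to 5.3 mg/kg, one would give 3.0 to 2.7.

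**The case against.** The strongest reply is that the dose is not hidden. The tables are the operative instruction, complete with weights, milligrams and tablet counts, and a phase III planner could copy them exactly. For AQ the conflict is between a figure in the summary and a fully specified body. The protocol has no rule that results must be reported under the stated mg/kg doses. No whole-tablet table can hit a target at every weight. Most of the AQ shortfall cannot be removed with whole tablets, and one tablet rather than two at 15 to 16 kg is defensible when adverse events are the primary endpoint.

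Much of this stands. The AQ upper row and the AS lower row are acceptable rounding and are not part of the point. MB is spread on both sides of its target, but its 10 mg/kg is equally unqualified and needs the same restatement. It does not answer the two one-sided rows, or the ratio, which makes the named comparator regimen unattainable at any weight.

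A reader might go further and infer that the comparator is underdosed, or that the comparisons of adverse events or ACPR are biased. The documents do not support that. They give no weight distribution, so the number of children affected is unknown, and nothing in them links these departures to outcomes. In each comparison with control the shared partner drug follows the same table in both arms: AQ for MB-AQ against AS-AQ, AS for MB-AS against AS-AQ. The drug that differs does follow its own table, but neither the direction nor the size of any effect can be derived.

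**Conclusion.** The point holds as a mismatch between stated and prescribed dose. AQ is below 10 mg/kg at every weight above 10.0 and up to 16.0 kg, by as much as 37.5%. AS is above 4 mg/kg at every weight from 16.5 to 22.5 kg, by 11% to 52%. No child in the AS-AQ arm can receive both stated doses.

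This rests only on the protocol's own tables, tablet strengths and weight limits, and assumes that children are dosed as the tables say. It should be corrected because the comparator is described by figures that the tables do not deliver. It is not a finding about bias, and the tables themselves need not change.

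**What to change.** **Recommended.** In the Protocol summary and in Description of the treatments, call the mg/kg doses nominal and add the delivered ranges: AQ 6.3–12.1 mg/kg daily, AS 3.1–6.1 mg/kg daily, MB 8.1–13.0 mg/kg per dose. Describe the comparator and the trial's conclusions by those ranges. The cost is wording only, with no added visits or samples.

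**Optional, only if the sponsor confirms that the 100 mg AQ and 50 mg AS tablets can be halved** (the protocol does not say):

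- AQ: 1 tablet for 10.0 to <12.5 kg (10.0 to 100/12.5 = 8.0 mg/kg); 1.5 for 12.5 to <17.5 kg (150/12.5 = 12.0 to 150/17.5 = 8.6); 2 for 17.5 to 22.5 kg (200/17.5 = 11.4 to 200/22.5 = 8.9). Overall 8.0–12.0 mg/kg; worst departure 20%.
- AS: 1 tablet for 10.0 to <15.5 kg (5.0 to 50/15.5 = 3.2 mg/kg); 1.5 for 15.5 to 22.5 kg (75/15.5 = 4.8 to 75/22.5 = 3.3). Overall 3.2–5.0 mg/kg; worst departure 25%.

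The price is tablet splitting at dosing, an extra AQ row, and different weight breaks for each drug in place of one shared break. The stated ranges would then be the new ones for AQ and AS, with MB unchanged.

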# Definitions

| Term | Definition |
| --- | --- |
| Baseline values | Directly after the written informed consent a blood sample will be taken for the baseline measurements (laboratory baseline values). |
| Age | The age is calculated using the date of informed consent and date of birth. If the day of the birth date is unknown, it is set to 15. If day and month are missing the 1st of July is considered as the date of birth. |
| D0, D1, D2, D3, D7, D14 and D28 | For the definition of days the latest WHO Definition is used (WHO 2003).  D0= calendar day of the first treatment, D1= first calendar day after the calendar day of first treatment. This definition is used for the endpoints ETF, LCF, LPF, ACPR and fever or parasite clearance time. D7, D14, D28 is defined as the 7th, 14th and 28th day after first drug intake, with a tolerance of –1 and +3 days. |
| ETF | - Danger signs or severe malaria on D1, D2 or D3 + parasitemia - Parasitemia on D2 > D0 count irrespective of axillary temperature - Parasitemia on D3 ≥ 25% of count on D0 |
| LCF | - Development of danger signs or severe malaria after D3 in the presence of parasitemia, without meeting any of the criteria of ETF - Presence of parasitemia + axillary temperature ≥37.5°C on any day from D4 to D28, without previously meeting any criteria of ETF |
| LPF | - Presence of parasitemia on any day from D7 to D28 + axillary temperature <37.5°C, without previously meeting any of the criteria of ETF |
| ACPR | - No parasites on D28 irrespective of axillary temperature without previously meeting any of the criteria of ETF, LCF or LPF |
| Fever clearance | Time between fever at inclusion and first temperature < 37.5°C |
| Parasite clearance | Time between inclusion and time where no more parasites are detectable |
| Recrudescence | Re-emerging of the same *P. falciparum* strain from D14 to D28 according to PCR genotyping |
| Reinfection | New infection from D14 to D28 according to PCR genotyping |
| AEs | The adverse event (=AE) defined in chapter 12 is used, but blue urine is expected for all children in the MB-AS and MB-AQ treatment groups. Only AEs after initiation of study treatment will be tabulated. |
| SAE | The definition of serious adverse event (SAE) is given in chapter 11 |
| Haemolysis | Any drop in haemoglobin (Hb) of >2.5 g/dl within 24 hours |
| Severe acute haemolysis | Hb  5 g/dl or received blood transfusion according to clinical judgement of study physician. |

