Therefore the ideal partner drug to MB still needs to be identified. Two studies have recently shown a synergistic effect of the drugs MB and AS in vitro and in rhesus monkeys (Akoachere et al. 2005, Barker et al. 2005). As both drugs are short acting and no resistance has been demonstrated so far, AS-MB appears to be a promising drug combination. However, to be useful under real life conditions in SSA such a combination needs to be highly effective in a three days regimen. Monotherapy with AS for three days achieved only low cure rates (between 20% and 50% on day 28) in nonimmune populations outside SSA (Borrmann 2003). However, only few studies have studied the efficacy of shorter regimens of AS monotherapy in SSA. While five day regimens of AS monotherapy reached rather high cure rates in semiimmune populations of Tanzania and Nigeria, a three days regimen conducted in 50 children aged 4-15 years with uncomplicated malaria in a hyperendemic area of Gabon had cured only 72% of children by day 28 (Borrmann 2003). However, in this study, the day 14 cure rate was still 92% and children developed mainly asymptomatic parasitaemia afterwards.

AQ alone has been shown to be still sufficiently effective in many areas of SSA where chloroquine is failing (Müller et al. 1996, Greenwood et al. 2005). The combination of AS-AQ has been shown to be highly effective in SSA (International Artemisinin Study Group 2002). AS-AQ together with artemether-lumefantrine have been chosen as the two new official first-line treatments of uncomplicated malaria in Burkina Faso since the year 2006. Thus, comparing the two MB-based combinations MB-AS and MB-AQ with the standard of care AS-AQ is important to judge the safety of these regimens in Burkina Faso and to provide first data on the comparable efficacy.

With effect of May 2006, the World Health Organisation has officially recommended to no longer using malaria monotherapy in the treatment of uncomplicated falciparum malaria (Nelson 2006).

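### The ban on other antimalarials runs to end of follow-up with no exemption for children who meet the protocol's own treatment-failure criteria

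*Protocol*

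**What the plan says.** Under Concomitant treatments, in the Protocol section Treatment of subjects and clinical study procedures, the rule is "All indicated drugs are allowed, except other western antimalaria drugs, antibiotics with antimalarial efficacy, acetanilide and phenacetin", followed by further drugs that might cause haemolysis. It holds "from beginning of treatment until end of follow-up". The one treatment that this subsection names for fever is that children at or above 38.5°C "will receive standard doses of paracetamol".

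The Definitions section sets failure criteria that need no danger sign or severe malaria:
- ETF can be met on parasite counts alone, for example "Parasitemia on D2 > D0 count irrespective of axillary temperature", or a D3 count of at least 25% of the D0 count.
- LCF is met by parasitaemia with a temperature of at least 37.5°C "on any day from D4 to D28, without previously meeting any criteria of ETF".
- LPF is "Presence of parasitemia on any day from D7 to D28" with a temperature below 37.5°C.

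Selection and withdrawal of subjects lets a child be withdrawn at the guardian's request or when, in the investigator's opinion, safety or ethics rules out further participation. Treatment failure is not named as a reason. The only compulsory withdrawal is for repeated vomiting of the first dose. Anyone withdrawn in the first 3 days is replaced.

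On national policy, the introduction (MB in the treatment of malaria) says: "AS-AQ together with artemether-lumefantrine have been chosen as the two new official first-line treatments of uncomplicated malaria in Burkina Faso".

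**The concern.** The trial tests two new combinations in children aged 3-4 years with falciparum malaria, so some failures must be expected. For such a child the protocol does more than stay silent: it states a prohibition that covers the whole time in which failure can be found. A physician who follows it literally must withhold any other antimalarial, withdraw the child, or deviate from the protocol. A safe course of care should not depend on a deviation.

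The second issue is what withdrawal does to the data. If an early failure is withdrawn so that the child can be treated, the replacement rule applies. Replacement then depends on an outcome of the trial, and the ETF rate is a secondary endpoint.

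**Working it through.** **Step 1. Does the ban cover every failure window?** The ban runs from first dose to end of follow-up (D28).

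| Criterion | Window | Inside the ban? | Danger sign needed? |
|---|---|---|---|
| ETF, danger signs or severe malaria with parasitaemia | D1-D3 | yes | yes |
| ETF, D2 count above D0 | D2 | yes | no |
| ETF, D3 count at least 25% of D0 | D3 | yes | no |
| LCF, danger signs or severe malaria with parasitaemia | after D3 | yes | yes |
| LCF, parasitaemia with at least 37.5°C | D4-D28 | yes | no |
| LPF, parasitaemia below 37.5°C | D7-D28 | yes | no |

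**Step 2. Does any other text lift it?**
- Clinical management of (serious) adverse events provides emergency medication for SAEs. The failures in the rows marked *no* need not be SAEs.
- Visits and treatment schedule tells guardians to bring a worsening child back to hospital, but names no antimalarial.
- Assessment of secondary endpoints cites the WHO 2003 document for determining response and failure rates, and Definitions cites it for the day count. Neither adopts it for managing failures.

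No exemption is stated.

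**Step 3. What may a child with LCF receive while in the trial?** Artemether-lumefantrine is not a study drug, so it is excluded on any reading. For artesunate, amodiaquine and methylene blue the text is ambiguous: the word *other* may mean other than the three study drugs, or other than the child's assigned regimen. No re-treatment rule settles it. Paracetamol starts at 38.5°C, so a child with parasitaemia and a temperature from 37.5°C to below 38.5°C is an LCF for whom this subsection names no treatment.

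**Step 4. Which failures can fall under the replacement rule?** The first 3 days are not defined in D0-D3 terms. No blood film is scheduled on D1. The one count-only criterion surely inside is therefore a D2 count above D0. The D3 criterion is inside only if D3 belongs to the first 3 days.

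**Step 5. Size for the ETF rate.** Input: 60 children per arm (Sample size, in Selection and withdrawal of subjects). If one ETF child is withdrawn, replaced and not analysed, and the replacement has no ETF, the arm's rate falls by

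1/60 = 0.0167 = 1.7 percentage points.

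This is the most that one child can contribute; if the replacement also has ETF, or if the replaced child stays in the analysis, the shift is zero.

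**Step 6. Illustration only.** The protocol gives no ETF rate. Let *f* be an assumed true rate and *w* the assumed share of ETF children who are withdrawn, replaced and left out, with replacements subject to the same process. The observed rate is *f*(1 − *w*)/(1 − *fw*). For *w* = 0.5:
- *f* = 2%: 0.010/0.990 = 1.0%
- *f* = 5%: 0.025/0.975 = 2.6%
- *f* = 10%: 0.050/0.950 = 5.3%
- *f* = 15%: 0.075/0.925 = 8.1%

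For *w* = 1 the observed rate is 0; for *w* = 0 it is *f*.

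**The case against.** The strongest reply is that the rule limits confounding drugs and is not meant to deny care. It stands under Concomitant treatments and opens by allowing all indicated drugs. A returning febrile illness fits the adverse-event definition, the adverse-event form records the therapy given, and guardians are told to come back. Withdrawal for safety or ethics is available, and nothing restricts treatment afterwards. Much of this stands. It makes it unlikely that a sick child would knowingly be left untreated, but none of these places names an antimalarial or lifts the ban.

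A reader might infer that withdrawal is the only way out. The documents do not support that. If *other* means other than the three study drugs, re-treatment with artesunate and amodiaquine, itself national first-line, could be open to a child still in the trial. That reading would, however, return children in the comparator arm to the regimen that had just failed.

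For LPF, whether to treat afebrile parasitaemia at once is a clinical choice. That is a reason to permit treatment rather than require it, and the febrile LCF case carries the point alone.

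It can also be said that the analysis of replaced children belongs to the statistical analysis plan, which is not at hand. That is correct, and it is why the ETF effect is stated as conditional. Drug permission, withdrawal and replacement are conduct rules, though, and an analysis plan cannot supply treatment that was not given. Consent pages are not shown and might describe care on failure; the visible ban would then conflict with them.

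**Conclusion.** The point holds as a defect in a conduct rule: the ban is explicit, spans every failure window and has no exemption for failures. It should be fixed, chiefly for safety. How many children it would affect cannot be derived from the protocol.

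The data effect is secondary and needs three things to happen together: an early failure is withdrawn, is replaced, and is left out of the analysis. The protocol orders only the second, and only once the first has happened. Under those assumptions the understatement of ETF is at most 1.7 percentage points per child in an arm of 60.

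Two stronger readings go too far. A biased ETF rate is not a certain consequence of the plan. Nor can a loss of adverse events be sized by counting missed visits. Assessment of primary endpoint describes continuous surveillance, with self-reported events included and examinations of all children to D28, so scheduled visits are not the unit of loss, and it is not stated that withdrawal ends observation.

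**What to change.** 1. **Concomitant treatments:** state that the ban ends once a child meets ETF, LCF or LPF, and that antimalarial treatment per national policy is then allowed. Say whether the study drugs may be used for this.
2. **Withdrawal criteria:** state that treatment failure is not a reason for withdrawal or replacement, and that the child counts as a failure in the randomised arm. Define the first 3 days in D0-D3 terms.
3. **Adverse events:** state that observation continues to D28 after failure, and flag events that start after rescue treatment. The flag is needed because the present rule is "Only AEs after initiation of study treatment will be tabulated", which would otherwise mix events under the study regimen with events after rescue.

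The cost is a few sentences in a protocol amendment and one extra item on the adverse-event form. No additional visits, samples or children are needed.
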